**Fig. 1 Fig1:**
[figure not shown]
Data flow in SEQUAR

We will use the matched dataset to test our hypotheses:

For H1a, CD outcome variables should be able to serve as surrogates (proxies) for rehabilitation treatment outcomes as measured by current best-practice assessment (PD outcome variables; see outcome assessment and study design in high-quality studies on the effectiveness of multidisciplinary orthopedic rehabilitation—e.g., [28]). For H1b, we assume at least a moderate correlation (> 0.30) between CD quality indicators and PD quality indicators. To test H2, the impact of cross-sectoral CD risk factors (on patient and facility levels) on current risk-adjustment models for quality assessment will be investigated.

### Study population and recruitment

#### Study 1: prospective longitudinal study

For study 1, ten German inpatient rehabilitation facilities (IRFs) were enlisted in the study by local representatives of the regional AOK health insurance funds, which in turn are recruiting a planned sample of 600 patients. Participating IRFs signed a collaboration agreement with the principal investigator, and each appointed a local study coordinator in charge of organization and implementation of all project tasks (e.g., recruitment of participants, distribution of patient information and consent forms, storing/safekeeping signed consent forms). Patient recruitment began in November of 2022 and will end in December 2023.

Patients eligible for participation are recruited on-site in the beginning of their orthopedic follow-up rehabilitation. Study coordinators present them with a physical copy of the study fact sheet (covering study synopsis, data protection, and other legal aspects), and ask for their participation. Those agreeing to participate sign an informed consent form. Eligibility is determined by meeting the inclusion criteria: Participants must be at least 18 years old at time of inclusion (beginning of rehabilitation), insured through AOK health insurance fund (for purposes of data availability), and receive inpatient orthopedic follow-up rehabilitation after implantation of a knee joint replacement or hip joint replacement due to osteoarthritis. Participants need to demonstrate sufficient knowledge of the German language and sufficient cognitive abilities to answer the comprehensive questionnaires independently. Patients that prematurely discontinue rehabilitation, demonstrate insufficient German or cognitive skills, or change health insurance within the study period will be excluded.

Participation in the study is incentivized with a €50 gift voucher for patients that complete all four questionnaires, while IRFs receive €120 per patient for full patient participation and completed case report forms.

#### Study 2: retrospective cohort study

Included in the study 2 sample will be all AOK-insured patients that underwent primary hip or knee arthroplasty due to osteoarthritis and participated in orthopedic inpatient follow-up rehabilitation between 2018 and 2023. Cases are identified in the SHI claims database using the diagnoses and procedures described in Table 1, based on the respective yearly version of the International Classification of Diseases 10, German Modification [29] and the German Operation and Procedure Codes (OPS, [30]).

**Table 1 Tab1:** Inclusion codes for retrospective cohort study

Procedures and diagnoses	Codes
Hip joint replacement	OPS: 5-820.0, 5-820.8, 5-820.9, 5-820.x
with discharge diagnoses	ICD-10: M05-M08, M16, M87
Knee joint replacement	OPS: 5-822.0, 5-822.g, 5-822.h, 5-822.j, 5-822.k
with discharge diagnoses	ICD-10: M05-M08, M17, M87

### Sample size

#### Study 1: prospective longitudinal study

Recruiting IRFs are encouraged to assess every patient for eligibility (as per the inclusion criteria), with a target sample of 60 participants per facility totaling *N* = 600 cases. Assuming an initial refusal quota of 30% (non-response), IRFs need to approach 860 patients, or 86 patients per facility. Withdrawal of consent or loss to follow-up throughout the data collection phase are estimated to result in an average dropout rate of 20% for each time point, which will reduce the initial target sample by approximately 50%. Thus, we expect a sample of n = 300 to remain for analysis (comparable studies report dropout rates of 25–55%, depending on the length of observational period; [31–33]). Figure 2 visualizes the sample flow in a CONSORT flow diagram.

**Fig. 2 Fig2:**
[figure not shown]
CONSORT flow diagram for study 1 (prospective longitudinal multicenter study)

#### Study 2: retrospective cohort study

Based on data from previous years, we expect around 27,000 patients nationwide participating in follow-up rehabilitation after knee joint replacement and 25,000 patients participating in follow-up rehabilitation after hip joint replacement, amounting to a study population of around 52,000 patients per year. Since study 2 includes patients from 2018 to 2023, the total study sample will be around 312,000 patients.

### Data collection

#### Study part 1: prospective longitudinal study

Data for the prospective multicenter study will be collected over a period of approximately 7 months with paper-pencil questionnaires. Patient-reported outcomes are recorded at four time-points: in the beginning of rehabilitation (baseline; t0), completion of rehabilitation (t1), three-month follow-up after completion (t2), and six-month follow-up after completion (t3). T0 and t1 patient questionnaires are to be distributed to patients a maximum of 2 days after inpatient admission and a maximum of 2 days before discharge by the local study coordinator. Patient questionnaires for t2 and t3 (follow-ups) are sent to patients’ residential addresses with prepaid return envelopes. IRF medical staff are to record additional medical data in a case report form at baseline (t0) and at completion of rehabilitation (t1).

#### Study part 2: retrospective cohort study

Claims data is sourced from the health claims databases of all 11 regional AOK health insurance funds. A project database will be compiled to include claims data from inpatient/hospital and outpatient care, medication, remedies and aids, as well as information on nursing care level and demographics. Additional data on the quality of the operating hospital is available through the established quality assurance procedure QSR [11]. The individual observation period for each patient includes 24 months before initial hospital admission and 12 months after follow-up rehabilitation. Figure 3 illustrates what data will be included in the project database and their statutory source in the German Social Code (see also section “Quality Assurance in German Rehabilitation”).

**Fig. 3 Fig3:**
[figure not shown]
Data compiled for and used in the retrospective cohort study. *Note*: All sections cited are from the German Social Code Book V, unless they are marked with *, in which case the governing statute is the German Social Code Book XI

### Study outcomes

#### Study 1: prospective longitudinal study

For study 1, the various outcomes and outcome domains are measured with different instruments and collected from different sources, as displayed in Table 2.

**Table 2 Tab2:** Outcomes, instruments, and data sources for study 1

Outcome (Domain)	Instrument	Data Source*	Time Point			
			t0	t1	t2	t3
Activities of daily living, emotional coping, mobility, physical functioning	Short Musculoskeletal Function Assessment (SMFA-D; [34])	P	x	x	x	x
Illness-related impairment/ “bother”	Short Musculoskeletal Impairment Assessment (SMFA-D; [34])	P	x	x	x	x
Physical pain	Visual Analogue Scale [35]	P	x	x	x	x
Pain-related self-efficacy	Pain Self-Efficacy Questionnaire (FESS; [36])	P	x	x	x	x
Walking ability	6 min Walk Test [37]	M	x	x		
Hip-specific outcome aspects such as limping, use of walkers, walking distance, climbing stairs, putting on shoes/socks	Harris Hip Score [38]	M	x	x		
Knee-specific outcome aspects such as mobility, stability	Knee Society Score [39]	M	x	x		
*Confounders*						
Comorbidity	Self-Administered Comorbidity Questionnaire (SCQ-D; [40])	P	x	x		
Age	Single item	P/M	x	x		
Gender	Single item	P/M	x	x		
Socio-economic status	Single item	P	x			
COVID-19-related stress	COVID-19 Stress Screening**	P	x			
Comorbidity	KOMO Score [41]	M	x			
Main and secondary diagnoses	ICD-10-GM codes [29]	M	x			

*P = patient-reported data, M = medical staff-reported data. **This instrument was developed by the principal investigator in 2020, publication is in progress. A translation of the adapted screening is attached in Additional File 1

#### Study 2: retrospective cohort study

Since study 2 is exploratory in nature, no CD outcomes have yet been identified. The following steps will be taken for selection and operationalization of CD outcome variables, CD quality indicators, and CD risk factors:

A structured search for existing quality indicators, outcome variables, and risk factors of orthopedic rehabilitation will be conducted in (a) literature (e.g., Medline, Cochrane Library), (b) medical guidelines (Guidelines International Network), (c) indicator databases (e.g., [42, 43], and (d) documentation of existing procedures of quality assurance in the field of orthopedic rehabilitation. Search results will be assessed for their compatibility with claims data.The nationwide project claims database of AOK-insured patients will be analyzed to identify additional complex healthcare and rehabilitation outcomes for patients that have undergone primary knee or hip arthroplasty. This includes analysis of demographics, medical and other relevant data such as comorbidities, nursing care level, medication use, and utilization of therapeutic health service. The database will encompass data from the individual observational period for each patient, which includes the 24 months pre-surgery as well as 12 months of care after orthopedic rehabilitation. Pre-surgery data will be used as a baseline measure of study population characteristics, while the follow-up period after rehabilitation can be used to identify individual changes in relation to the baseline.Results from step (1) and (2) will be consolidated and CD outcomes and risk factors operationalized. Potential CD outcomes that represent aspects of rehabilitation treatment quality within claims data could be, for example, mobility (through provision of mobility aids), pain medication, or progression to higher nursing care levels. CD outcomes will consider care and quality aspects from all medical sectors. All quality indicators will be defined by denominators and numerators, and descriptions of inclusion, exclusion and exception criteria [44]. Denominators display a specified target population (e.g., all patients undergoing arthroplasty), whereas numerators display the number of people in the target population experiencing a specified outcome (e.g., surgical complications; [44]). These descriptive definitions can later be used to calculate individual values for rehabilitation facilities. Indicators will be translated into coded data (e.g., coded diagnoses, procedures, and prescriptions), and an appropriate reference value will be defined for each indicator.Each CD quality indicator will be adjusted for risk factors that have statistical influence on the indicator rate but cannot be influenced by IRFs. Risk factors might include patient characteristics (e.g., age, sex, comorbidity, nursing care level), or aspects of acute hospital care before rehabilitation. Relevant risk factors will be selected based on current research, results from SHI data analyses, and expert opinion [45].

### Data analysis and hypothesis testing

#### Study 1: prospective longitudinal study

Missing values analysis will be performed for each variable. If the results support the assumption of values missing at random or completely at random, they will be imputed via multiple imputation. Within the framework of sensitivity analysis, the hypotheses will be tested with both the raw dataset and the imputed dataset.

##### Hypothesis 1

To test hypothesis H1, the PD outcome variable dataset collected in study 1 will be matched to the CD outcome variable dataset using participants’ national health insurance numbers, which are pseudonymized by a data trustee in accordance with German data protection laws. Three dimensions of diagnostic validation will be evaluated to assess whether the CD variables can serve as proxies for the PD variables (see section “Study outcomes”): accuracy, reproducibility, and precision [46].

Accuracy will be assessed by linear regression, with each PD outcome variable as a dependent and each CD outcome variable as an independent variable. 95% confidence intervals (CIs) will be calculated for the identified intercepts and regression coefficients using the Gaussian approach (95%-CI of a: a ± 2*Se_a_; 95%-CI of b: b ± 2*SE_b_). If the CIs include 0 and 1 (for intercepts and regression coefficients, respectively), accuracy will be considered adequate for the outcome variable.

Reproducibility will be assessed by duplicate standard deviation (SD), which is calculated using the following formula (with *d* as the individual difference between the CD outcome variable and approximated PD outcome variable for each patient):$$\varvec{D}\varvec{u}\varvec{p}\varvec{l}\varvec{i}\varvec{c}\varvec{a}\varvec{t}\varvec{e} \varvec{S}\varvec{D}=\sqrt{1/2\left(\frac{\sum {\varvec{d}}^{2}}{\varvec{n}}\right)}$$

Following the recommendation by Cleophas & Zwinderman [46], reproducibility is considered adequate for a duplicate SD of 10–20%.

Precision will be assessed by comparing the standard deviations of CD outcome variable and approximated PD outcome variable. If the standard deviation of a CD outcome variable is equal or smaller to the standard deviation of an approximated PD outcome variable, precision is considered good or better.

If at least two of the three validation criteria are met, the tested CD outcome variable is considered an adequate proxy for the respective PD outcome variable. Bland-Altman plots will be used for graphic evaluation of measurement differences [47, 48]. This same procedure will be applied to test H1b using CD quality indicators and PD quality indicators, which are represented by facility group mean values of PD outcome variables.

##### Hypothesis 2

H2 postulates an improvement in risk-adjustment models when considering cross-sectoral claims data, i.e., an increase in (adjusted) R^2^, and will be analyzed with nested multilevel regression models. A basic model (M0) will be estimated for each PD outcome variable using the PD confounders (see Table 2) on level 1. Models will be estimated for each time point after baseline (t1, t2, t3), and will be adjusted for *time* (rehabilitation effect) as a predictor on level 2. Furthermore, level 2 PD quality indicators will be included. Each model will be expanded with previously identified CD risk factors (on level 1 and level 2) as described in section “Study outcomes”. The nested models will be compared with Likelihood Ratio tests [49]. The analysis sample will be randomly divided into two parts, with one half allocated for analysis of risk-adjustment, and the remaining half used to validate the resulting models.

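### Multiple imputation in study 1 depends on the data supporting missing at random, which observed data cannot do; about 49% loss is expected by t3

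*Protocol article*

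**What the plan says.** In the protocol article, under Data analysis and hypothesis testing, Study 1, the missing-data plan has three steps.

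- A check: "Missing values analysis will be performed for each variable". The article names no test or threshold.
- A rule: "If the results support the assumption of values missing at random or completely at random, they will be imputed via multiple imputation".
- A sensitivity analysis: "the hypotheses will be tested with both the raw dataset and the imputed dataset".

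The article does not state what follows if the check is judged not to support either assumption. It also does not say which of the two datasets carries the main conclusion.

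Under Sample size, Study 1, it assumes an "average dropout rate of 20% for each time point", puts the overall loss at about half, and concludes: "Thus, we expect a sample of n = 300 to remain for analysis". The Limitations section adds that dropout is a known problem six months out. It also concedes that leaving out patients who die may understate poor outcomes and fit sicker patients badly.

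**The concern.** Whether values are missing at random or not at random depends on the values nobody has seen. A missing values analysis can show that missingness is related to observed variables, which counts against missing completely at random. It cannot show that, given those variables, missingness is unrelated to the unseen outcome.

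The rule imputes under either of the two milder mechanisms, so the one distinction the data can inform does not change the decision. The distinction that does decide it is untestable. Whether imputation goes ahead is then a matter of judgement after the data are seen.

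If that judgement is negative, the article names no analysis other than the raw data. Suspecting not-at-random loss would thus lead to an analysis that does nothing about it. If the judgement is positive, the raw and imputed results are compared, but neither models not-at-random loss, so their agreement says nothing about robustness to it.

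At stake are the study 1 quantities that depend on who returns the later questionnaires. These are t3 outcomes, the facility means that serve as primary-data (PD) quality indicators in H1b, and the standard deviations compared in the precision criterion.

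**Working it through.** **Inputs from the article:** target sample 600 in ten facilities (60 each); 20% dropout per time point; four time points (t0 to t3), hence three transitions; stated remainder 300.

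**Step 1: reproduce the stated figure.** Remaining = 600 × (1 − 0.20)^k after k transitions.

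| Time point | k | Remaining | Loss |
|---|---|---|---|
| t1 | 1 | 480 | 20% |
| t2 | 2 | 384 | 36% |
| t3 | 3 | 307 | 49% |

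The t3 row (307.2, loss 48.8%) agrees with the stated 300 and the stated loss of about half. Per facility it leaves 60 × 0.8³ ≈ 31 of 60.

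**Step 2: precision.** With only returned t3 data, the standard error of a mean is sqrt(600/307) = 1.40 times that of full data. If an earlier score correlates 0.5 with the t3 outcome (assumed), imputing on it brings this to about 1.40 × sqrt(1 − 0.25 × 0.49) = 1.31.

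**Step 3: can the check tell the mechanisms apart?** This is a simulation on assumed values: N = 600, 50% missing at t3, correlation 0.5 between an observed earlier score and the t3 outcome, 2,000 runs. The check is a t-test of the earlier score by missingness. Imputation is by regression on that score. Bias is that of the t3 mean, in SD.

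| Mechanism (log-odds of missingness per SD) | Check significant | Bias, imputed | Bias, raw |
|---|---|---|---|
| At random, earlier score, 0.125 | 34% | 0.00 | −0.03 |
| Not at random, t3 outcome, 0.25 | 33% | −0.09 | −0.12 |
| At random, earlier score, 0.25 | 86% | 0.00 | −0.06 |
| Not at random, t3 outcome, 0.5 | 82% | −0.18 | −0.23 |

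Within each pair the check behaves almost identically, yet imputation is unbiased in the first row and biased in the second. The raw-data mean is biased in all four rows.

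At a not-at-random log-odds of 1.0 the biases are −0.32 (imputed) and −0.41 (raw). Across the three not-at-random settings, imputation on one earlier score removes about a quarter of the raw bias (0.12 to 0.09, 0.23 to 0.18, 0.41 to 0.32).

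**Step 4: a simple scale for a mean.** Bias of the completer mean = share missing × difference between dropouts and completers. At t3, assumed differences of 0.2 and 0.5 SD give 0.49 × 0.2 = 0.10 SD and 0.49 × 0.5 = 0.24 SD. The article supplies no such difference. This is the bias of a mean, not of the association between PD and claims-data (CD) outcomes.

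**The case against.** The case for leaving the plan alone has real substance.

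- **Both analyses are planned.** If imputation goes ahead, raw-data results are reported beside it, and a missing values analysis can usefully identify predictors of dropout. A reader might infer that the whole estimate hangs on an uninformative check. That is too strong: the check is uninformative only for the decision it is given.
- **Complete cases are not always worse.** A regression on complete cases is valid when missingness depends only on its covariates. In H1a the PD outcome is regressed on the CD outcome, and claims do not depend on returning a questionnaire. If dropout depends only on the CD predictor, intercept and slope stay unbiased. This stands. Means and standard deviations do not share that protection in general.
- **49% is the t3 figure.** The walk test and the hip and knee scores are taken only at t0 and t1, and the H2 models are fitted at each time point. The raw dataset need not mean patients complete through t3.
- **A common shift leaves the H1b correlation unchanged.** Only dropout that differs between facilities would move it, although a shift could affect the intercept criterion, which is also applied to H1b.
- **Claims data are not excluded from the imputation.** The article lists no imputation variables, and a condensed article may leave that to a fuller document. One cannot infer that the linked claims go unused.
- **Recovery-related dropout is plausible but not documented.** The concession about deaths concerns excluded patients, not questionnaire return.
- **Not all the loss can be imputed.** It includes withdrawn consent, and deaths and insurance changes are handled by exclusion.

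These points limit the consequences. None of them makes the stated condition testable, and the condition is the article's own text, not an omission.

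**Conclusion.** The point holds as a fault in a stated rule: imputation is made to depend on a condition that the data cannot establish, and the stated sensitivity analysis does not examine the alternative. It should be corrected; it does not invalidate the study.

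Its weight grows with the loss, from 20% at t1 to 36% at t2 and 49% at t3, on the article's own dropout assumption. It is greatest for t3 outcomes, facility means and standard deviations.

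That the mechanisms cannot be told apart does not rest on the simulation values; every bias figure does. A reader might infer that the PD–CD association is biased by 0.10 to 0.24 SD, or is estimated only in patients who recovered better. The documents support neither: the figure concerns a mean under an assumed difference, and no direction of dropout is reported.

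**What to change.** Delete the condition and state missing at random as an assumption of the analysis. Then:

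- Make multiple imputation, or a likelihood mixed model, the primary analysis for participants whose data may still be linked and used.
- Put earlier scores, the Table 2 confounders, facility and the linked post-discharge claims variables in the imputation model. The article plans claims follow-up for 12 months after rehabilitation, so these can inform t2 and t3 for patients who stop returning questionnaires.
- Keep the missing values analysis, but use it to choose predictors of missingness.
- Add a delta-adjusted (not-at-random) sensitivity analysis over a stated range, reported for the H1a, H1b and H2 criteria.
- Keep the raw-data analysis as secondary.

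The cost is wording, code and some extra analysis work; no new data are needed. Imputation will recover only part of the lost precision (a ratio of about 1.31 instead of 1.40 in the example above) and remove only part of any not-at-random bias, which is why the delta-adjusted analysis is needed.

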#### Study part 2: retrospective cohort study

Data of patients who switch health insurance or decease within their individual observation period will be censored from claims data.

The claims database with be analyzed with descriptive statistics, more precisely summary statistics (measures of central tendency, spread, and dispersion), and frequency distributions. We use stratified analyses and multivariate modelling (logistic regression and generalized linear models) to estimate the influence of potential risk factors. The data structure requires multi-level regression models for cluster effects: On a patient level, we estimate the influence of case-mix variables (e.g., age, sex, comorbidity, nursing care level) on each specified outcome within a potential CD quality indicator (see section “Study outcomes”). On a facility level, we estimate the influence of quality of acute hospital care on each specified outcome within a potential CD quality indicator.

The existence of further cluster effects at IRF level will be explored. CD quality indicators will only be adjusted for risk factors an IRF has no control over, e.g., a patient’s age. Relevant measures to assess goodness-of-fit for logistic regression models are Hosmer-Lemeshow-test, Receiver Operating Characteristic (ROC Curve), Area under the curve (ROC AUC) and pseudo-R2 [50]. For general linear models, a robust estimator for estimation of covariance matrix is used.

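### The H1a accuracy test ignores clustering of patients in ten facilities, so its intercept interval is too narrow if facilities differ after conditioning on the claims variable

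*Protocol article*

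**What the plan says.** In the Protocol article, Data analysis and hypothesis testing, Hypothesis 1, the accuracy criterion is fully specified.

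- **Model:** "Accuracy will be assessed by linear regression, with each PD outcome variable as a dependent and each CD outcome variable as an independent variable".
- **Interval:** "95% confidence intervals (CIs) will be calculated for the identified intercepts and regression coefficients using the Gaussian approach", written out as the estimate ± 2 SE for both intercept and slope.
- **Rule:** accuracy is adequate when the intercept interval includes 0 and the slope interval includes 1.

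Accuracy is one of three criteria, beside reproducibility and precision. Two of the three make a claims (CD) variable an adequate proxy for the primary-data (PD) variable.

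The patients are clustered. Under Study population and recruitment, "ten German inpatient rehabilitation facilities (IRFs) were enlisted in the study", and Sample size plans recruitment "with a target sample of 60 participants per facility". For H2, on these same patients, the risk-adjustment question "will be analyzed with nested multilevel regression models". Nothing comparable is stated for H1a. A robust covariance estimator is named only for study 2 and is not described as cluster-robust. No ICC is given anywhere.

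**The concern.** A single-level regression with the usual SE treats the roughly 300 analysed patients as independent. Patients of one facility share staff, programme and case mix. Any part of that which shows in the PD outcome, but not in the CD variable, becomes a shared residual. The usual SE leaves it out, and it acts mainly on the intercept.

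The interval is a pass/fail device here, so its width matters directly. An interval that is too short misses 0 more often than its nominal rate, even when the proxy is exact (intercept 0, slope 1). The loss grows with the residual differences between facilities. The Discussion says that failure to find suitable claims indicators would support keeping the questionnaires as best practice, so wrongly failing a good variable has a consequence.

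**Working it through.** **1. The plan's sample flow, which sets the cluster size.**
- Approached: 600 / (1 − 0.30) = 857; the article says 860.
- Retained, with an "average dropout rate of 20% for each time point" over three follow-up points: 600 × 0.80³ = 307; the article says 300.
- Both agree within rounding. This gives 300 / 10 = 30 patients per facility. The Study design section also splits the matched data into an analysis and a validation subsample. If that means halves and covers H1a, m = 15.
- The article has no power or precision figure for H1a to reproduce.

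**2. Nominal coverage.** 2Φ(2) − 1 = 95.4%.

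**3. Intercept when zero is the mean of the CD variable.** The variance is understated by D = 1 + (m − 1) × ICC(residual). The true coverage of ± 2 SE is 2Φ(2/√D) − 1. The ICCs are assumptions.

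| m | ICC | D | √D | Coverage |
|---|---|---|---|---|
| 30 | 0.01 | 1.29 | 1.14 | 92% |
| 30 | 0.05 | 2.45 | 1.57 | 80% |
| 30 | 0.10 | 3.90 | 1.97 | 69% |
| 15 | 0.01 | 1.14 | 1.07 | 94% |
| 15 | 0.05 | 1.70 | 1.30 | 87% |
| 15 | 0.10 | 2.40 | 1.55 | 80% |

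**4. Slope.** The factor is 1 + (m − 1) × ICC(predictor) × ICC(residual). With m = 30 and both ICCs 0.05: 1 + 29 × 0.0025 = 1.07, SE ratio 1.04, coverage 95%. With both 0.10: 1 + 29 × 0.01 = 1.29, SE ratio 1.14, coverage 92%. With predictor ICC 0 there is no inflation.

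**5. Intercept when zero lies k predictor SDs from the mean.** The factor is (D + k² × slope factor) / (1 + k²). With k = 2 and m = 30:
- ICCs 0.05: (2.45 + 4 × 1.0725) / 5 = 1.35, SE ratio 1.16, coverage 91–92%.
- ICCs 0.10: (3.90 + 4 × 1.29) / 5 = 1.81, SE ratio 1.35, coverage 86%.

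**6. Simulation** (ten facilities, truth a = 0 and b = 1, least squares with ± 2 SE, equal ICC in predictor and residual).
- Continuous CD variable centred at zero, m = 30: intercept coverage 80% (ICC 0.05) and 69% (0.10). Both intervals pass in 75% and 64%, against 91% without clustering.
- Zero 2 SD from the mean, m = 30: intercept coverage 91–92% and 87%. Both pass in 89% and 83%, against 93%.
- Binary CD variable, m = 30: intercept coverage about 94% (ICC 0.01), 87% (0.05) and 79% (0.10). Both pass in 84% (0.05) and 75% (0.10), against 92% without clustering.
- With m = 15, intercept coverage is about 94%, 87–90% and 80–84% at ICC 0.01, 0.05 and 0.10 for a centred continuous or a binary variable.
- Slope coverage stays at 92–95% at m = 30.

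**7. The remedy in the same setting.** Cluster-robust SEs with t on 9 degrees of freedom bring intercept coverage back to about 94–96%. The intercept interval becomes roughly 1.3 to 2.1 times as wide at ICC 0.05–0.10. For a proxy biased by 0.3 residual SD with m = 30 and ICC 0.05, the accuracy pass rate rises from about 2–4% to about 15–20%.

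**The case against.** **The size is conditional.** No ICC is given, and at 0.01 the loss is only 0 to 4 points. Only the residual ICC matters: a claims variable that itself carries the facility differences leaves less behind, and one that does not is a doubtful proxy for comparing facilities. This stands as a limit on size. It does not remove the point, because H1a asks about the average patient-level relation, and that interval is wrong under any positive residual ICC. The binary setting, with slope 1 against a scale score, is artificial and only illustrates.

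**The article is condensed.** It says linear regression, not ordinary least squares, and does not name the SE estimator; a fuller document might. But it does fix the model, interval multiplier and pass rule, and followed as written these contain no allowance for facility.

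**Study 2 is weak support.** One might cite "The data structure requires multi-level regression models for cluster effects" as the article's own admission. That sentence concerns the nationwide claims data, and the facility effect named with it is acute hospital care. Cluster effects at rehabilitation-facility level are left there to be explored. The inconsistency rests on H2 alone.

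**Stronger readings that do not hold.** A reader might infer that slope intervals are equally too narrow; step 4 shows they are not. A reader might also infer that poor proxies are wrongly accepted. Under a rule that passes when the interval includes the target value, a short interval errs towards rejection. Nor are the both-pass figures rates of final proxy acceptance, since a variable that fails accuracy can still qualify on the other two criteria.

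**The fix loosens the gate.** This stands. Wider intervals include 0 and 1 more easily, and for a project meant to replace questionnaires wrong acceptance may be the worse error. The inclusion rule has no equivalence margin, and a correct SE does not supply one.

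**Conclusion.** The point holds in a limited form. H1a accuracy is specified as a single-level regression with ± 2 SE on patients nested in ten facilities, while H2 models that nesting. With a positive residual ICC the intercept interval is too narrow.

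At 30 patients per facility and assumed ICCs of 0.01, 0.05 and 0.10, its coverage is about 92–94%, 80–87% and 69–79%. At 15 per facility it is about 94%, 87–90% and 80–84%. These ranges are for a binary CD variable or one with zero at its mean. The loss is smaller where zero lies far from the usual CD values: about 87% at ICC 0.10, 30 per facility and 2 SD.

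The consequence is that a correct proxy fails one of three criteria too often. How often that changes final acceptance cannot be computed from the article, but the effect is smaller than these figures. It is a correctable flaw in a decision interval and does not invalidate H1a as a whole.

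**What to change.** Add to Hypothesis 1 that each H1a regression is fitted with a random intercept for facility, or with cluster-robust (CR2) SEs. Replace ± 2 SE with a small-cluster t reference (Satterthwaite or Kenward-Roger degrees of freedom), because there are only ten clusters. Report the residual ICC for each PD outcome. State whether the analysis/validation split applies to H1a, since it sets the cluster size.

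The change needs one or two sentences, a standard software option and no new data. The real cost is width: the intercept interval grows by roughly 1.3 to 2.1 times at ICC 0.05–0.10, and biased proxies then meet the accuracy criterion more often. The plan should say so, and should report the intercept, the slope and their interval widths beside every pass/fail result, so that a pass from a wide interval is not read as evidence of agreement.
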